### Sample size

PolypESS is a superiority trial in which disease-specific HRQOL, measured with the SNOT-22 at 12-month follow-up, is the primary outcome of interest. The sample size calculation is build on the literature-based assumption that the minimal clinically important difference (MCID) for SNOT-22 is 8.9 points (SD 20.0) [18]. Using a 5% significance level and a power of 90% yields a sample size of 238 patients, which includes a 10% anticipated loss to follow-up.

### Randomisation

A randomisation sequence is generated using block sizes of 6 stratified by study centre. A central, password-protected, consistently available automated randomisation system (ALEA® software, Trans European Network for clinical trial services (TenALEA) consortium, Amsterdam, The Netherlands) has been developed by the independent Clinical Research Unit in the Academic Medical Centre, Amsterdam, The Netherlands. Due to the nature of both interventions, blinding is not possible.

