### Study design

The PolypESS is an investigator-initiated, prospective, open, national, multicentre randomised controlled trial investigating the (cost-)effectiveness of ESS in patients suffering from CRSwNP. Suitable patients will be randomised into two treatment groups. In the first group patients will undergo ESS in addition to medication, in the second group patients will receive an intensified drug treatment only. Total follow-up is 24 months for all included consecutive patients. Otorhinolaryngologists in the participating centres are asked to recruit patients. Any patient who meets the inclusion criteria (described in detail below in ‘Study population’ section) will be informed about the trial and asked to participate. The coordinating trial centre (Academic Medical Centre, Amsterdam, The Netherlands) will contact patients who have expressed interest in the trial. The study team member will provide detailed written and oral information about the trial and answer any questions. If patients agree to participate, inclusion and exclusion criteria will be checked and a baseline visit will be scheduled. Potential participants have sufficient time before they give their final consent to participate in the trial. If patients decline participation, known clinical data on disease-specific HRQOL and objective signs of disease are used to evaluate whether the findings of the consecutive sampling are generalisable to the target population. The trial reporting is according to the CONsolidated Standards of Reporting Trials (CONSORT) guidelines and the CONSORT extension for nonpharmacological interventions (Fig. 1) [14, 15]. The Standard Protocol Items: Recommendations for Interventional Trials (SPIRIT) 2013 Checklist: ‘Recommended items to address in a clinical trial protocol and related documents’, can be found in Additional file 1. The SPIRIT participant schedule is shown in Table 1.

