### Setting

The trial is performed in 15 hospitals, three university-affiliated hospitals (The Academic Medical Centre, Amsterdam; Erasmus Medical Centre, Rotterdam; VU Medical Centre, Amsterdam) and teaching hospitals (Amstelland Hospital, Amstelveen; Alrijne Hospital, Leiderdorp and Alphen aan den Rijn; BovenIJ Hospital, Amsterdam; Deventer Hospital, Deventer; Flevo Hospital, Almere; Haga Hospital, Den Haag; Onze Lieve Vrouwe Gasthuis location East, Amsterdam; Onze Lieve Vrouwe Gasthuis location West, Amsterdam; Spaarne Hospital, Hoofddorp; Spaarne Hospital, Haarlem; Tergooi Hospital, Hilversum and Blaricum; and Westfries Gasthuis, Hoorn) in The Netherlands. The same medical researcher and research nurses perform all trial assessments in the participating centres, apart from nasal endoscopy. Nasal endoscopy is performed by the local ENT surgeon as part of standard care.

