### Patient enrolment

Selection of patients follows a two-stage procedure. Consecutive patients are screened for eligibility by a recruiting local otorhinolaryngologist in the outpatient department. Additionally a telephone interview is scheduled by the medical researcher in the Academic Medical Centre during which eligibility will be reassessed. Patients will be enrolled by the medical researcher during a clinic visit in the concerning hospital. Patients meeting all inclusion criteria and no exclusion criteria can be included and will be randomly assigned, after informed consent is given.

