### Interventions

Patients will be assigned to a surgical strategy (ESS in addition to drug treatment) or a drug treatment strategy exclusively. Clinicians and patients will not be blinded to the treatment arm of the study. Those assigned to surgery will be offered ESS within 6 weeks of randomisation. Those assigned to drug treatment will be seen by the otorhinolaryngologist within 6 weeks of randomisation to define the need for additional medication. As this is a pragmatic trial, ESS refers to the surgery performed regularly by otorhinolaryngologists in The Netherlands. The extent of surgery is tailored to the extent of the disease. Drug treatment comprises any usual care medication.

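### A single block size of 6 within each centre, published during recruitment of an open trial, weakens allocation concealment: about 19% to 23% of allocations can be deduced

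*Protocol article*

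**What the plan says.** The Randomisation section of the protocol article gives one block size and one stratification factor: "A randomisation sequence is generated using block sizes of 6 stratified by study centre". It describes a central, access-controlled automated system developed by an independent Clinical Research Unit, and says that blinding is not possible. The Interventions section confirms the open design: "Clinicians and patients will not be blinded to the treatment arm of the study".

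On who controls entry, the Patient enrolment section says that, after screening by the local otorhinolaryngologist, "a telephone interview is scheduled by the medical researcher in the Academic Medical Centre during which eligibility will be reassessed", and then: "Patients will be enrolled by the medical researcher during a clinic visit in the concerning hospital". The Setting section adds: "The same medical researcher and research nurses perform all trial assessments in the participating centres, apart from nasal endoscopy".

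The Trial status section reports that recruitment was in its first phase, with completion expected in Summer 2017. The block size was therefore made public while patients were still being randomised.

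**The concern.** Concealment requires that whoever decides on entry cannot foresee the next arm. With a constant, known block size, the remaining places in a block are certain once one arm has filled its half. In an open trial, anyone who follows the allocations at a centre can see when that happens. Here one role is placed to do so at every hospital, and that role also re-checks eligibility and enrols.

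There is room for judgement at entry. The Study population section contains exclusions that call for interpretation, such as an overriding need for surgery or an illness that would prevent adequate participation. If foreknowledge influenced such decisions, or the timing of the enrolment visit, the arms could differ in prognosis before treatment began. Intention-to-treat analysis does not correct that. Nor does the response to baseline imbalance in the Statistical methods section, which is subgroup analysis.

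**Working it through.** **Inputs.** Block size 6, with centre as the only stratum (Randomisation). 238 patients, target difference 8.9 points, SD 20.0, 90% power, 5% significance level, 10% loss (Sample size). Centres: "The trial is performed in 15 hospitals" (Setting). The allocation ratio is not stated; the Study design section says only "Suitable patients will be randomised into two treatment groups". I assume 1:1, that is 3:3 per block, which fits 238 = 2 × 119.

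**1. The plan's own figure.** Two-sided, n per arm = 2 × (1.960 + 1.282)² × 20² / 8.9² = 106.1, rounded up to 107. Then 214 / 0.90 = 237.8, rounded up to 238. This agrees with the article, and the point made here does not affect it. The article gives no figure for predictability.

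**2. One complete block.** There are 20 equally likely 3:3 sequences. A place is certain once one arm has used its three.
- Place 4: the first three are alike, 2/20 = 0.10.
- Place 5: the first four split 3:1, 8/20 = 0.40.
- Place 6: always, 1.00.

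The sum is 1.5 of 6, or 25%. The closed form 2m/(m + 1) with m = 3 gives the same.

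**3. Incomplete last blocks.** 238/15 = 15.9, so take 13 centres of 16 and 2 of 15.
- 16 patients: 2 × 1.5 + 0.10 = 3.1 (19.4%).
- 15 patients: 2 × 1.5 + 0 = 3.0.
- Total: 13 × 3.1 + 2 × 3.0 = 46.3 of 238 = 19.5%.

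Centres will not be equal. A simulation with assumed gamma-distributed centre weights gave 21.8% on average, with 95% of runs between 20.8% and 22.8%. The range is therefore about 19% to 23%, or about 46 to 54 patients.

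**4. Best guess rather than certainty.** Guessing the arm with more places left is right with probability 0.5, 0.6, 0.6, 0.7, 0.7 and 1.0 at places 1 to 6. That is 4.1/6 = 68.3% per complete block. For 16 patients it is (2 × 4.1 + 2.4)/16 = 66.3%.

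**5. Possible bias.** Bias = share deduced × prognosis gap between those steered to each arm. The documents give no gap, so I assume 2 to 8 SNOT-22 points, and that every deducible allocation is recognised and acted on.
- Low end: 0.195 × 2 = 0.4 points.
- High end: 0.228 × 8 = 1.8 points.

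Against the 8.9-point target these are about 4% and 20%.

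**6. Effect of varied block sizes.** Simulated for 16 patients per centre, with an observer who knows the set of sizes and updates on every past allocation:

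| Block sizes | Certain allocations | Best-guess rate |
|---|---|---|
| 6 only | 19.4% | 66.3% |
| 4 and 6 | 5.9% | 68.3% |
| 4, 6 and 8 | 2.5% | 66.9% |

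Varied sizes remove most of the certainty. They do not lower the guess rate of someone who knows the set.

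**The case against.** The other side has good arguments. The list is held centrally by an independent unit, and most allocations, about 77% to 81%, are never certain. The rest can be known only to someone who knows the block size and keeps a tally by centre. The article also describes safeguards: consecutive patients are screened, criteria are checked before the baseline visit is scheduled, reasons for exclusion are registered, assignment follows consent, and clinical data on patients who decline are used to check generalisability. The surgeon's approach to the patient comes up to 10 weeks ahead in Table 1, before the visit with randomisation, so foreseeing the arm at referral is harder.

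All of this stands as a limit on the size of the problem. It does not remove it. A central system cannot hide what can be counted, the size needed for counting is in print, and the safeguards record steering better than they prevent it.

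Three stronger readings are tempting, and the documents do not support them.
- A reader might infer that concealment is defeated, with a quarter of allocations, or about 4 per centre, known in advance. The 25% holds only for complete blocks. Certain places come late in a block, so 16 patients yield 3.1, and these are knowable rather than known.
- A reader might infer that the enrolling researcher favours surgery. The preference in the Background section is that of Dutch otorhinolaryngologists; none is documented for the researcher.
- A reader might infer an actual bias of some 2 points. That needs a large assumed gap applied to the complete-block share, and no steering is shown.

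**Conclusion.** The point holds as a weakness in allocation concealment, not as evidence of bias. Assuming 1:1 allocation, someone who knows the block size and tallies allocations by centre can deduce about 19% to 23% of them with certainty. The possible bias of about 0.4 to 1.8 SNOT-22 points illustrates a worst case in which all deducible allocations are acted on; it is not an estimate. A change is worthwhile because it is cheap and recruitment was still open.

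**What to change.** For patients still to be randomised, the independent Clinical Research Unit should load a new list with randomly varied block sizes within centre, for example 4, 6 and 8 in random order. The sizes, and the set from which they are drawn, should be withheld from site staff and the enrolling researcher and kept out of publications until recruitment ends. Given the unchanged best-guess rate in the table above, non-disclosure is an essential part of the fix. The actual set should therefore not be taken from any public comment, this one included.

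For patients already randomised, the analysis plan that the Statistical methods section promises before database lock should add a sensitivity analysis of the primary outcome that excludes the deducible allocations. These can be identified from the list and the order of entry at each centre.

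The cost is a new list in the existing system and a short amendment. Balance within a centre may be slightly worse: a part-filled block of 6 can be at most 3 out of balance, one of 8 at most 4, and a block abandoned at the switch can leave up to 3. The sensitivity analysis loses some precision because it drops patients.

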### Statistical methods

#### Primary data analysis

Results will be based on the intention-to-treat method. In addition, per-protocol analysis, including only patients who adhered completely to the clinical trial instructions and treatment specified in the protocol, will also be performed to check the robustness of results. Continuous normally distributed variables will be expressed by their mean and standard deviation or, when not normally distributed, as medians and their interquartile ranges. Categorical variables will be expressed as counts (*n*) and percentages (%). Effects on HRQOL, nasal endoscopy and symptom score will be calculated as mean differences with 95% confidence intervals. HRQOL, short- and long-term effects will be additionally evaluated at 3, 6, 12, 18 and 24 months’ follow-up, respectively. It is expected that randomisation will balance patients’ baseline characteristics. However, if imbalances occur between groups that are related to possible effect modification, subgroup analyses will be performed according to the indication for surgery.

A further detailed statistical analysis plan will be developed and reported by the chief investigators prior to the database being locked at the end of follow-up for final analysis.

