### Baseline measurements

On the day of enrolment, patients will undergo the same HRQOL and objective evaluation, including the SNOT-22, the EuroQol-5D-5L questionnaire (EQ-5D-5L, the EuroQol Group) and nasal endoscopy, that will be used after treatment (see “Outcomes” section). Clinical data is collected by the enrolling medical researcher and focuses on the (severity of) patient-reported symptoms, previous clinical examinations, previous sinonasal surgery, previous conservative treatment and complete medical history. Demographic variables include age, gender, ethnicity, marital status, family situation and highest level of education. Additional study information includes the presence or absence of asthma, acetylsalicylic acid (ASA) intolerance, allergy, occupational exposure, smoking habits and alcohol consumption. Objective measurements recorded are baseline height, weight, blood pressure, resting heart rate, total IgE, serum eosinophil level and computed tomography (CT) scores using the Lund-Mackay scoring system. This system uses a 0–1–2 score dependent upon absent, partial or complete opacification, respectively, of each individual sinus and the ostiomeatal complex, contributing to a maximum score of 12 per side. The total score of the two sides can reach a maximal 24 points [16]. A urine pregnancy test will be performed in female patients with childbearing potential if in doubt of pregnancy.

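### The protocol answers baseline imbalance with subgroup analyses instead of a pre-specified estimate adjusted for baseline SNOT-22 and centre, which gives up precision in the primary comparison

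*Protocol article*

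**What the plan says.** Under Sample size, the protocol article states: "PolypESS is a superiority trial in which disease-specific HRQOL, measured with the SNOT-22 at 12-month follow-up, is the primary outcome of interest". The calculation there takes it that "the minimal clinically important difference (MCID) for SNOT-22 is 8.9 points (SD 20.0"), and continues: "Using a 5% significance level and a power of 90% yields a sample size of 238 patients, which includes a 10% anticipated loss to follow-up". No baseline correlation enters.

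Under Primary data analysis, the effect measure is given in one sentence: "Effects on HRQOL, nasal endoscopy and symptom score will be calculated as mean differences with 95% confidence intervals". No test, model or covariate is named. The section then says "It is expected that randomisation will balance" the patients' baseline characteristics. The one response to imbalance is subgroup analysis by indication for surgery, and only for imbalances connected with possible effect modification. The section ends by promising a detailed statistical analysis plan before the database is locked at the end of follow-up.

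Two other sections show what is available for adjustment. Baseline measurements: "On the day of enrolment, patients will undergo the same HRQOL and objective evaluation, including the SNOT-22". Randomisation: "A randomisation sequence is generated using block sizes of 6 stratified by study centre". Under Setting: "The trial is performed in 15 hospitals".

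**The concern.** A baseline measurement of the outcome is usually among the best predictors of that outcome later, and this trial has one. Leaving it out of the primary analysis widens the confidence interval for no saving. Centre is built into the allocation, so a standard error that ignores it does not match the design.

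The rule for imbalance is the more definite weakness, because it is stated and not merely left open. Two different problems are run together:

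- An imbalance in a prognostic factor moves the overall estimate. Covariate adjustment deals with it.
- Effect modification means that the effect differs between kinds of patient. Interaction or subgroup analysis deals with it.

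The protocol applies the second tool to the first problem. Splitting by indication for surgery leaves the overall 12-month difference exactly as it was. The rule is also triggered by the imbalance observed, so it depends on the data. The trial is open, and the analysis plan is due only before a lock that follows 24 months of follow-up. A covariate set chosen that late could be chosen after 12-month results have accrued.

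**Working it through.** **Inputs from the protocol.** Difference 8.9, SD 20.0, 5% significance, 90% power, 10% loss, total 238 (Sample size). Stratification by centre (Randomisation), 15 hospitals (Setting). Two-sided testing and 1:1 allocation are not stated; both are assumed because they reproduce the total.

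**Inputs assumed.** The correlation r between baseline and 12-month SNOT-22, range 0.3 to 0.7. The share of variance between centres (ICC), range 0.01 to 0.10. The documents give neither.

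**1. The protocol's own figure.**
n per arm = 2 × (1.96 + 1.2816)² × 20² / 8.9² = 106.1, rounded up to 107. Total 214, and 214 / 0.9 = 237.8, rounded up to 238. This matches exactly. A one-sided test would give 87 per arm and does not match. So 238 is the size for a plain two-sample comparison, and 90% power is met without any adjustment.

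**2. Precision without adjustment.**
SE = 20 × √(2/107) = 2.73. Half-width = 1.96 × 2.734 = 5.36 points. Power for 8.9 points is 90.2% by the normal formula.

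**3. Precision with baseline adjustment.**
Residual SD = 20 × √(1 − r²), with 107 per arm.

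| r (assumed) | Residual SD | SE | Half-width | Power | Unadjusted / adjusted variance |
|---|---|---|---|---|---|
| 0 | 20.0 | 2.73 | 5.36 | 90.2% | 1.00 |
| 0.3 | 19.1 | 2.61 | 5.11 | 92.7% | 1.10 |
| 0.5 | 17.3 | 2.37 | 4.64 | 96.4% | 1.33 |
| 0.7 | 14.3 | 1.95 | 3.83 | 99.5% | 1.96 |

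**4. What a chance imbalance does.**
If the baseline SD is also 20 (assumed), the between-arm baseline difference has SE 2.73. A difference of one SE moves the unadjusted estimate by r × 2.73, which is 0.8, 1.4 or 1.9 points at r = 0.3, 0.5 or 0.7. At the edge of the 95% range (5.36) and r = 0.5, the shift is 2.7 points, or 30% of 8.9. This is the same variance as in step 3 seen from another side, not an additional loss.

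**5. Leaving out centre.**
The true SE is the reported SE × √(1 − ICC). For ICC 0.01 to 0.10 the factor is 0.995 to 0.949. The actual type I error is then 2 × [1 − Φ(1.96 / √(1 − ICC))], about 4.9% down to 3.9%. Adjusting for centre alone gives power of 90.5% to 92.9%.

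**6. If SD 20.0 belongs to a change score.**
The protocol does not say which it is. With equal variances at both times, the score variance is 400 / [2(1 − r)], so the adjusted residual SD is 20 × √((1 + r)/2): 16.1, 17.3 or 18.4 at r = 0.3, 0.5 or 0.7. Half-widths are 4.32, 4.64 or 4.94. They are still below 5.36, which in this case is the half-width of an unadjusted analysis of change. The gain remains, but it then shrinks as r rises.

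**The case against.** The strongest reply is that the protocol never calls the effect unadjusted. A mean difference with a 95% confidence interval is also what ANCOVA or a mixed model yields, so the quoted sentence is compatible with the adjustment asked for here. Model and covariates are usual content of the analysis plan, which the protocol promises and which is not shown. That stands: the missing covariate list by itself is no finding, and an unadjusted primary analysis is an inference. It is the best-supported one, because the effect measure, the reliance on expected balance, the subgroup fallback and the plain two-sample sample size all point the same way. The deferral does not rescue the subgroup rule, which is written down and cannot do what is needed.

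Three stronger readings are tempting and are not supported:

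- **That the primary estimate would be biased or the trial underpowered.** Randomisation makes the unadjusted difference unbiased, chance imbalance is random error already inside the interval, and the planned power is met.
- **That ignoring centre invalidates the test.** The error is small and on the conservative side.
- **That patients without a 12-month score are dropped, with attrition bias.** The protocol states intention to treat and gives no missing-data rule, so nothing says that they are excluded.

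It is also fair to say that the gain is modest at low correlation: at r = 0.3 the half-width falls by only 0.25 points.

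**Conclusion.** The point holds in a limited form. What the protocol fixes is a mean difference that relies on expected balance, with a subgroup rule that leaves prognostic imbalance in the overall estimate. If it is carried out as it most naturally reads, the analysis is valid and has its planned power, but it is less precise than the collected data allow. The half-width would be about 5% wider than necessary at r = 0.3 (5.36 / 5.11 = 1.05), 16% at r = 0.5 (5.36 / 4.64 = 1.16) and 40% at r = 0.7 (5.36 / 3.83 = 1.40). These sizes rest on an assumed correlation, on 107 evaluable patients per arm, and on SD 20.0 being that of the 12-month score. The centre effect is minor. This is a free improvement that should be made, not a condition for the trial's validity.

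**What to change.** In Primary data analysis, state that the primary estimate is the treatment difference in SNOT-22 at 12 months, with 95% confidence interval, adjusted for baseline SNOT-22 and centre. ANCOVA or a mixed model will serve. Centres will average about 16 randomised patients (238 / 15), and some will be smaller, so say in advance that very small centres are pooled or that centre is a random effect. Report the unadjusted difference as supportive.

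Replace the rule that answers imbalance with subgroup analyses. Keep subgroup analyses for effect modification only, chosen in advance and not triggered by observed imbalance.

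The cost is a few sentences. No new data, visits or patients are needed, and the sample size can stay at 238. The wording should be fixed before any 12-month comparison by arm is seen.

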**Methods:**

A prospective, multicentre, superiority, randomised controlled (PolypESS) trial in 238 patients aged 18 years or older selected for primary or revision endoscopic sinus surgery by the otorhinolaryngologist was designed. Patients will be randomised to either endoscopic sinus surgery in addition to medication or medical therapy only. Relevant data will be collected prior to randomisation, at baseline and 3, 6, 12, 18 and 24 months after start of treatment. Complete follow-up will be 24 months. Primary outcome is disease-specific Health-related Quality of Life quantified by the SNOT-22 after 12-month follow-up. Secondary outcomes are generic Health-related Quality of Life, cost-effectiveness, objective signs of disease and adverse effects of treatment. Subgroup analyses will be performed to verify whether treatment effects differ among patient phenotypes.

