## Methods

### Study objectives

The primary aim of the PolypESS trial is to assess the effectiveness of ESS in addition to drug treatment as compared to drug treatment alone in adults with CRSwNP in terms of improving patients’ HRQOL, measured by the Sinonasal Outcome Test 22 (SNOT-22) at 12-month follow-up. Key secondary aims of the trial are evaluation of the effectiveness of ESS in addition to drug treatment as compared to drug treatment alone in the short (3–6 months) and long (12–24 months) term, in terms of generic HRQOL, objective signs of disease and adverse effects of treatment. This trial will also evaluate which patient phenotypes within CRSwNP benefit from ESS in addition to drug treatment as compared to drug treatment alone. Furthermore, the relation between health care resource use and patient costs and effects of ESS will be determined from a societal point of view. It is hypothesised that a more tailored approach for patients with CRSwNP will be associated with lower medical and indirect costs (health care utilisation and productivity loss).

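### The imbalance-triggered subgroup rule neither corrects a chance imbalance nor tests effect modification, and it does not match the unconditional phenotype aim

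*Protocol article*

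**What the plan says.** The Protocol article, under Primary data analysis, expects randomisation to balance the arms and then adds a contingency: "if imbalances occur between groups that are related to possible effect modification, subgroup analyses will be performed according to the indication for surgery". It gives no criterion for imbalance, does not define indication for surgery, and names no covariate adjustment. Effects are described as mean differences with 95% confidence intervals. The only other subgroup statement in the analysis sections is a general one in the cost analysis.

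Elsewhere the subgroup question is posed differently and without condition. The abstract says: "Subgroup analyses will be performed to verify whether treatment effects differ among patient phenotypes". Study objectives says: "This trial will also evaluate which patient phenotypes within CRSwNP benefit from ESS in addition to drug treatment".

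Randomisation uses "block sizes of 6 stratified by study centre", so no clinical factor is balanced by design. A further detailed analysis plan is promised before database lock.

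**The concern.** The sentence joins two separate problems and gives an answer that fits neither.

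- **Imbalance.** If the arms differ by chance on a prognostic factor, the observed treatment difference carries part of that factor's effect. The remedy is to adjust for the factor. Splitting the sample by a different variable leaves the difference in place.
- **Effect modification.** Whether the effect of surgery differs between types of patient is a treatment-by-factor interaction. It may be present in perfectly balanced arms and absent in unbalanced ones. Observed imbalance is therefore not a sensible condition for looking for it.

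The rule is also hard to square with the stated aims. The abstract and objectives speak of phenotypes. The statistical methods speak of indication for surgery, in a population where every participant has already been selected as a surgical candidate, so it is unclear what its levels would be. The article's discussion says that the results should lead to a tailored strategy and selective use of surgery, so the subgroup question deserves a rule that addresses it.

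**Working it through.** **1. The plan's own figure.** Inputs from Sample size: difference 8.9 points, SD 20.0, 5% significance (two-sided assumed, as sidedness is not stated), 90% power, 10% loss. Equal allocation is assumed.

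n per arm = 2(1.960 + 1.282)² × 20² / 8.9² = 106.1, rounded up to 107. Allowing for loss: 107/0.90 = 118.9, so 119 per arm and 238 in total. This agrees with "a power of 90% yields a sample size of 238 patients" and is not in dispute. It gives 107 analysable patients per arm for what follows.

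**2. Does splitting remove an imbalance?** Assumptions, none of them from the documents: one baseline covariate with correlation 0.5 to the outcome; an imbalance at nominal p<0.05; a subgroup factor unrelated to that covariate, split 50:50.

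Expected size of the imbalance, in covariate SDs, given that it passes the threshold:
- mean of |Z| beyond 1.96 = 2 × 0.0584/0.05 = 2.34
- standard error of the difference in covariate means = √(2/107) = 0.137
- product = 0.32 SD

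Shift in the SNOT-22 difference = 0.32 × 0.5 × 20 = 3.2 points.

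A simulation of 20,000 trials, of which 4.89% (978) met the threshold, gave these mean shifts in the direction of the imbalance:

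| Analysis | Shift (points) |
|---|---|
| Unadjusted difference | 3.3 |
| Split by the unrelated factor, two strata averaged | 3.3 |
| Adjusted for the covariate | 0.1 |

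The Monte Carlo standard error is about 20 × √0.75 × √(2/107) / √978 = 0.08, so 3.3 agrees with the derived 3.2, and 0.1 is within noise of zero. Splitting does nothing for the imbalance and adjustment removes it.

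**3. Do the statements on subgroups agree?**

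| Place | Condition | Factor |
|---|---|---|
| Abstract, Methods | none | patient phenotypes |
| Study objectives | none | patient phenotypes |
| Primary data analysis | observed imbalance | indication for surgery, undefined |

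They differ in both condition and factor. The analysis section contains no clinical rule that carries out the first two.

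**4. What the sample can say about an interaction.** This bears only on how the phenotype results should be labelled. For a 50:50 factor, each of the four cells has 53.5 patients:
- SE = 20 × √(4/53.5) = 5.47 points
- detectable at 80% power = (1.960 + 0.842) × 5.47 = 15.3 points

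With a 30% or 20% subgroup share, the detectable difference rises to 16.7 or 19.2 points.

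**The case against.** The strongest reply is that the sentence is a contingency, not an exclusive rule. It does not say that subgroups are examined only after imbalance, or only by indication for surgery. The phenotype statements in the abstract and objectives remain in force, and a later analysis plan can name factors and models. This stands in large part. A reader might infer that, followed as written, the phenotype aim is dropped unless the arms happen to differ. The text does not support that; it shows a mismatch that needs reconciling, not a flat contradiction. Nor is it a fault that the article gives no phenotype list or interaction model.

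Three other tempting readings also go too far.

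- **That indication for surgery is not collected.** Baseline measurements include previous sinonasal surgery, symptoms and medical history, and eligibility covers primary and revision surgery. The term may mean one of these. It is undefined, not shown to be unrecorded.
- **That the trigger will usually fire by chance.** Testing 20 independent variables at 5% would give 1 − 0.95²⁰ = 64%. But the plan names no test and restricts the trigger to imbalances linked to possible effect modification. With six variables the same formula gives 26%. Neither figure measures this rule.
- **That low interaction power is a harm done by the rule.** Power depends on the trial's size and would be the same under any better rule.

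It is also fair to say that chance imbalance does not bias a randomised comparison across repetitions, and that its standard error allows for it. The shift of about 3 points is conditional on a notable imbalance and on the assumed correlation. Finally, if indication for surgery were itself the unbalanced factor, an estimate combined over its levels could reduce the imbalance, but the plan specifies no such combination.

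What the reply does not answer is that the article states a rule. A further detailed plan must either follow that rule or depart from it.

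**Conclusion.** The point holds as a flaw in a stated rule. The response to imbalance does not correct imbalance, the condition for examining effect modification is not a valid one, and the single factor named is undefined. The rule does not match the unconditional phenotype analyses promised elsewhere, though it does not rule them out.

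The size is moderate. In a trial with a clear imbalance in a covariate correlated 0.5 with the outcome, about 3 points would remain in the overall estimate, against a design difference of 8.9. A weaker correlation or a smaller imbalance would leave proportionately less. The rest of the argument is logical and needs no assumption.

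A reader might infer that the primary result is invalid without this change. It is not: the intention-to-treat comparison is valid on average whether or not the trigger fires. This should be fixed, but it is not a condition for the trial to stand.

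**What to change.** - Delete the imbalance trigger.
- State in advance that the primary SNOT-22 comparison at 12 months is adjusted for baseline SNOT-22, centre (the stratification factor) and a small set of prognostic factors already recorded, whatever imbalance is observed.
- Carry out the phenotype analyses unconditionally, as treatment-by-factor interactions with 95% confidence intervals. Fix the factors before outcome data are seen; candidates already collected include primary or revision surgery, asthma and ASA intolerance. The final list and coding can sit in the analysis plan.
- Label these analyses exploratory, and say why: for an evenly split factor, only an interaction of about 15 points is detectable with 80% power.
- Define indication for surgery, or drop it, and bring the abstract, the objectives and the analysis section into line.

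The cost is a change of wording and slightly more analysis work. It needs no new data and no change to the sample size.
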